# Talking in primary care (TIP): protocol for a cluster-randomised controlled trial in UK primary care to assess clinical and cost-effectiveness of communication skills e-learning for practitioners on patients’ musculoskeletal pain and enablement

**DOI:** 10.1136/bmjopen-2023-081932

**Published:** 2024-03-19

**Keywords:** Primary Health Care, eHealth, MEDICAL EDUCATION & TRAINING, Musculoskeletal disorders, Patient-Centered Care

## Abstract

**Introduction:**

Effective communication can help optimise healthcare interactions and patient outcomes. However, few interventions have been tested clinically, subjected to cost-effectiveness analysis or are sufficiently brief and well-described for implementation in primary care. This paper presents the protocol for determining the effectiveness and cost-effectiveness of a rigorously developed brief eLearning tool, EMPathicO, among patients with and without musculoskeletal pain.

**Methods and analysis:**

A cluster randomised controlled trial in general practitioner (GP) surgeries in England and Wales serving patients from diverse geographic, socioeconomic and ethnic backgrounds. GP surgeries are randomised (1:1) to receive EMPathicO e-learning immediately, or at trial end. Eligible practitioners (eg, GPs, physiotherapists and nurse practitioners) are involved in managing primary care patients with musculoskeletal pain. Patient recruitment is managed by practice staff and researchers. Target recruitment is 840 adults with and 840 without musculoskeletal pain consulting face-to-face, by telephone or video. Patients complete web-based questionnaires at preconsultation baseline, 1 week and 1, 3 and 6 months later. There are two patient-reported primary outcomes: pain intensity and patient enablement. Cost-effectiveness is considered from the National Health Service and societal perspectives. Secondary and process measures include practitioner patterns of use of EMPathicO, practitioner-reported self-efficacy and intentions, patient-reported symptom severity, quality of life, satisfaction, perceptions of practitioner empathy and optimism, treatment expectancies, anxiety, depression and continuity of care. Purposive subsamples of patients, practitioners and practice staff take part in up to two qualitative, semistructured interviews.

**Ethics approval and dissemination:**

Approved by the South Central Hampshire B Research Ethics Committee on 1 July 2022 and the Health Research Authority and Health and Care Research Wales on 6 July 2022 (REC reference 22/SC/0145; IRAS project ID 312208). Results will be disseminated via peer-reviewed academic publications, conference presentations and patient and practitioner outlets. If successful, EMPathicO could quickly be made available at a low cost to primary care practices across the country.

**Trial registration number:**

ISRCTN18010240.

STRENGTHS AND LIMITATIONS OF THIS STUDYAssessment of a brief online learning package that is evidence-based and theory-based and was rigorously developed with primary care clinicians.Practitioners (eg, general practitioners, physios and nurses) consult as usual without needing to identify or obtain consent from patients within the consultation, as patient recruitment is done by administrative staff.Focused on patients with musculoskeletal pain but including other patients as ‘all-comers’ enables an efficient test of relevance to all primary care consultations.Feasibility work showed it is not practicable to record consultations in this trial, so there is no direct assessment of changes in practitioner communication behaviours after engaging with the e-learning package.‘All-comers’ is a large and varied group of patients that enhances generalisability but is not suitably powered to plan subgroup analyses.

## Introduction

Approximately 1.7 billion people worldwide have musculoskeletal conditions, which are typically painful, limit people’s daily lives and impair quality of life.^1^ Musculoskeletal conditions, including back, hip, knee and neck pain, are commonly managed in primary care,^2–4^ where patient-centred care, including excellent practitioner–patient communication, is an international priority.^5–7^ In the UK, people with musculoskeletal conditions may be seen in primary care by general practitioners (GPs), practice nurses, physiotherapists and other allied healthcare professionals.

Regardless of which treatment, therapy or other intervention a patient receives, effective practitioner–patient communication can reduce symptoms and enhance quality of life, adherence to and satisfaction with care, producing benefits comparable to many pharmaceutical interventions.^8–10^ Suboptimal communication can lead to missed opportunities for benefit, worse quality of life and symptom management, unwanted prescriptions and non-adherence,^11 12^ unnecessary economic costs,^12^ deviations from guideline-recommended treatment^13^ and increased complaints and litigation.^14 15^ Despite communication skills being taught in medical and allied health professional training, patients still report dissatisfaction with practitioner–patient communication.^16 17^ The extent to which patients rate their practitioners as being empathic varies widely^18^ and medical students appear to exhibit broadly stable or declining levels of empathy during their degrees.^19 20^ The need to enhance and expand communication skills is particularly pertinent since the COVID pandemic forced the rapid introduction of remote consultations, bringing new opportunities and challenges for patients and staff not specifically trained to consult in this way.^21^

We focus on the communication of clinical empathy and positive messages within primary care consultations. Clinical empathy and positive messages are not routinely reliably optimised in clinical care but can have statistically and likely clinically significant effects on pain, patient satisfaction and other outcomes with no evidence of adverse effects.^22^ Our intervention planning determined that enhancing practitioners’ communication of clinical empathy and realistic optimism was feasible, measurable and likely to have a significant impact.^23 24^ Even brief interventions can improve communication skills, including interventions concentrating on empathy skills such as active listening and expressing warmth at appropriate times,^25–27^ which take no additional time in the consultation.^27 28^ However, few interventions have been tested clinically for effects on patients’ health,^29^ subjected to formal cost-effectiveness evaluations^30^ or are sufficiently brief and well-described to facilitate implementation in the current primary care climate. Our work aims to address these limitations. We are evaluating the effects on patients’ health of brief, evidence-based, online training to enhance practitioners’ communication of clinical empathy and realistic optimism within everyday clinical consultations (‘EMPathicO’).

## Aims and objectives

The primary objective is to determine EMPathicO’s effects on (1) patient-reported pain and (2) patient enablement via repeated measures over 6 months following the index consultation in patients presenting with musculoskeletal pain, compared with usual care control.

This clinical focus on musculoskeletal pain was chosen to align with the EMPathicO training, which includes modules on clinical empathy, realistic optimism and how to communicate these better in the context of consultations for osteoarthritis. Including a condition-specific module permitted a clear demonstration of communication skills in a particular context, which made the training better targeted and potentially more effective.^31^ A painful musculoskeletal condition was chosen because much (but not all) of the evidence that underpins the importance of clinical empathy and realistic optimism for patient outcomes is derived from studies of pain and painful conditions; osteoarthritis was chosen because it is a prevalent painful musculoskeletal condition in primary care.

Secondary objectives are as follows.

To estimate EMPathicO’s cost-effectiveness and effects on patient-reported quality of life and other secondary outcomes, over 6 months from index consultation, in patients with musculoskeletal pain.To test hypothesised mechanisms of action.To explore EMPathicO’s potential for implementation, by:Determining EMPathicO’s effects on patient enablement, patient-reported quality of life and other secondary outcomes over 6 months from index consultation, in patients ineligible for the musculoskeletal pain group (ie, presenting with other symptoms and/or very low levels of musculoskeletal pain, hereafter referred to as ‘all-comers’). This group was included because clinical empathy and realistic optimism may be beneficial for many different symptoms seen in primary care, and when practitioners adopt new communication behaviours within consultations for one type of condition, these skills may ‘spill over’ and also be implemented in consultations for other conditions. We wanted to evaluate any such additional benefits.Identifying opportunities, barriers and solutions for widespread implementation and impact, using the RE-AIM framework to explore EMPathicO’s Reach, Effectiveness, Adoption, Implementation and Maintenance.^32 33^

## Methods and analysis

This protocol is reported in accordance with the Standard Protocol Items: Recommendations for Interventional Trials checklist (online supplemental material 1).^34^ The first site was randomised on 31 October 2022, and data collection is due to finish on 31 July 2024.

10.1136/bmjopen-2023-081932.supp2Supplementary data

### Patient and public involvement

To ensure our work engages and is relevant to patients, we have worked with patients and members of the public throughout the development of EMPathicO and this protocol. We continue working closely with our Patient Advisory Group, led by our patient and public involvement and engagement lead (PPIE), JB, who sits on our trial management group. Our Patient Advisory Group comprises six patient and public contributors of varying ages, ethnic backgrounds (three from black and minority ethnic backgrounds and three from white backgrounds), gender (three females and three males) and geographical locations within England. One member is neurodivergent, and all have lived experience of musculoskeletal pain as patients or carers. Our panel meets virtually for 1 hour bimonthly and contributes to specific activities, including refining patient-facing documents and procedures, training qualitative interviewers and interpreting data.

### Design

A cluster-randomised controlled parallel group superiority trial in primary care, with embedded qualitative and mixed-methods process and implementation analyses.

Cluster randomisation was chosen because randomising individual practitioners risks cross-contamination within practices where practitioners share knowledge and patients; randomising individual patients risks contamination because practitioners cannot switch on/off communication skills in different consultations.

General practices constitute the clusters; practices are recruited and then randomised 1:1 EMPathicO:control. Randomisation is stratified (see below). All eligible practitioners within clusters are encouraged to undertake EMPathicO training (intervention) or consult patients as usual (control). The control was chosen to enable a pragmatic assessment of the benefits and costs of adding EMPathicO training to usual care.

Patient recruitment commences at least 2 weeks after the general practice is randomised (enabling time for intervention sites to complete the intervention training while maintaining consistent set-up timelines across both arms). All adults (18+) verbally consulting a participating practitioner are invited to participate in the trial (see exclusions below).

Two groups of patients are recruited. The musculoskeletal group comprises patients consulting participating practitioners about musculoskeletal pain. The ‘all-comer’ group comprises patients consulting about symptoms other than musculoskeletal pain (or reporting very low levels of musculoskeletal pain). At preconsultation baseline and repeatedly up to 6 months later, patients complete questionnaires assessing pain, enablement and secondary outcomes.

### Setting

General practices in England and Wales are recruited and supported by three recruitment hubs: Southampton, Keele and Bristol.

### Target population

#### GP practice eligibility criteria

*Eligible*: National Health Service (NHS) general practices in England and Wales, where a general practice is ‘an organisation which offers primary care medical services by a qualified general practitioner who can prescribe medicine and where patients can be registered and held on a list’.^35^

*Excluded*: practices involved in intervention development and feasibility work (18 from Wessex and 5 from the West Midlands), practices where clinical members of the trial management group or trial steering committee (TSC) see patients.

#### Practitioner eligibility criteria

*Eligible*: practitioners from any discipline who are working within participating GP surgeries and seeing patients with musculoskeletal pain (eg, GPs, practice nurses, physiotherapists, pharmacists and physician associates).

*Excluded*: practitioners unwilling to undertake the intervention or trial procedures.

#### Patients with musculoskeletal pain eligibility criteria

For the musculoskeletal pain group, eligible patients are adults (18+); verbally consulting a participating practitioner about new, recurrent or ongoing musculoskeletal pain (eg, back, hip, upper or lower extremity, neck pain—consistent with the International Classification of Diseases-11th edition’s diseases of the musculoskeletal system^36^); reporting average pain in the last week as four or more on a numerical rating scale at baseline (0=no pain; 10=pain as bad as you can imagine); consulting face-to-face, telephone or videoconference and able to give informed consent. The first consultation is the ‘index’ consultation, an initial triage interaction does not constitute an ‘index’ consultation. People without English as a first language are eligible; interpreters are available to support access to trial paperwork and patient-reported measures, and their use is recorded; informal interpreters (eg, family) may also provide support.

*Excluded*: patients consulting solely in written forms (eg, e-consult or email), pain caused by malignancy, being unable to consent or to complete questionnaires (eg, severe mental illness or distress and terminal illness), already enrolled in the trial (ie, from a previous consultation) and aged<18.

#### All-comer patients’ eligibility criteria

For the all-comers group, eligible patients are adults (18+); verbally consulting a participating practitioner about something other than musculoskeletal pain or consulting for musculoskeletal pain and rating average pain in the last week as less than four at baseline and able to give informed consent.

*Excluded*: as for patients with musculoskeletal pain.

### Interventions

#### EMPathicO e-learning package

EMPathicO is an evidence-based, theoretically grounded digital e-learning package for practitioners routinely seeing patients frontline in primary medical care, including GPs, nurse practitioners and first-contact physiotherapists.^24^ EMPathicO helps practitioners enhance their communication of clinical empathy and realistic optimism, is consistent with major consultation models including Ideas, Concerns and Expectations (ICE)^37^ and incorporates behaviour change techniques. Using the Behaviour Change Wheel, EMPathicO was designed to target users’ motivation (reflective and autonomic), capability (physical and psychological) and opportunity (environmental) through the intervention functions of persuasion, incentivisation, enablement, education, training, modelling and environment restructuring. Multiple behaviour change techniques were used to achieve these functions, including demonstration, information provision, goal-setting, action planning and instruction. For a complete behavioural analysis of EMPathicO, see supplementary material in our intervention development paper.^24^

The brief interactive e-learning modules are completed by practitioners and can be completed separately or together in less than 75 min. They cover clinical empathy, realistic optimism, tailoring empathy and optimism for patients with osteoarthritis (a common cause of musculoskeletal pain), evaluating one’s own consultations and goal-setting. The structure and contents of the modules are summarised in figure 1. EMPathicO was developed using LifeGuide open-source software for creating online interventions for healthcare, health promotion and training.^38^

**Figure 1 F1:**
[figure not shown]
Schematic summary of EMPathico structure and contents.

The systematic process of developing EMPathicO using the person-based approach^39^ involved multiple literature reviews, behavioural analysis and extensive iterative qualitative research.^40–46^ This work all contributed to the underpinning logic model (figure 2).^24^

**Figure 2 F2:**
[figure not shown]
Logic model showing how EMPathicO is hypothesised to affect patient outcomes.

#### Control: usual care

Practitioners in practices randomised to usual care control do not receive training and are asked to consult as usual. They are offered access to EMPathicO after all patient recruitment and follow-up are completed.

#### Concomitant interventions

All practitioners are discouraged from undertaking additional communication skills training during the study and must self-report any that does occur.

### Recruitment

#### GP practice recruitment

Practices are recruited with local Clinical Research Network support, seeking practices of different sizes (small and large) and locations (urban and rural) and those serving populations in areas of higher deprivation and greater ethnic diversity.

#### Practitioner recruitment

Practitioners within participating practices are recruited by that practice’s lead for this study (the local principal investigator) with support from the trial team and materials including an infographic and 1-min video explaining the study.

#### Patient recruitment

Practices invite into the study consecutive patients who are consulting participating practitioners within the recruitment period, after screening out any patients who do not have the capacity for consent or where there are medical grounds for excluding the patient (eg, very unwell generally and severe mental distress). Patient recruitment methods are tailored to suit individual practices’ appointment booking systems. For patients with prebooked or same-day appointments, practices text, email or post a brief invitation and link to the patient-facing study website up to 1 week before their consultation. Practices screen potential invitees for initial eligibility before sending invitations. Practices may display a poster in practice and/or on their website. Reception staff may introduce the study to patients attending in person. Patients email or phone the patient-facing research team with questions.

Practices follow their usual procedures for contacting non-English speakers to invite them to take part, for example, contacting a designated friend, relative or support worker, arranging an interpreter or adding a sentence in the patient’s own language on the initial study invitation.

The number of patient invitation emails or texts sent by each site is collected and recorded centrally. Qualtrics records instances of patients accessing the study website but declining consent and/or not meeting inclusion criteria.

The patient-facing study website is hosted on Qualtrics and shows the full study invitation and patient information sheet (PIS) (in languages requested by practices). After reading the PIS, patients complete a brief screening questionnaire, online consent and baseline measures. Online supplemental material 2 contains PIS and consent forms.

10.1136/bmjopen-2023-081932.supp3Supplementary data

### Sample size

#### Patients with musculoskeletal pain sample size

The minimum clinically important difference in the pain primary outcome is approximately one point,^47^ SD 3.3, consistent with a standardised effect size of 0.3. For 90% power, an alpha of 0.025 to allow for two primary outcomes, and a correlation between the four repeated measures of 0.7, a sample size of 214 per group is required. We assume a conservative intraclass correlation coefficient (ICC) of 0.03, at the upper 75% of what has been observed in previous primary care trials.^48^ Assuming 20 patients per practice gives a design effect of 1.57. Allowing for a 20% loss to follow-up gives a total sample size of (214*2*1.57)/0.8=840 participants to be recruited from 42 practices.

#### ‘All-comer’ patients’ sample size

Recruiting 840 all-comers will give 90% power (based on alpha and ICC as per the musculoskeletal group above) to detect a standardised effect size of 0.3 in the enablement primary outcome, equivalent to a difference of 0.36 points (assuming SD=1.2^49^).

#### Updated sample size calculation

Participants are being recruited from 53 practices rather than 42 practices as originally planned, which reduces the average cluster size. Assuming 14 patients per practice gives a design effect of 1.39. Under the same assumptions as above, the total sample size is (214*2*1.39)/0.8=744 participants.

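### The updated total of 744 makes no allowance for unequal numbers of patients per practice, and the text does not say whether it replaces the published target of 840

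*Protocol article*

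**What the plan says.** The musculoskeletal sample size section takes 90% power, "an alpha of 0.025 to allow for two primary outcomes", "SD 3.3, consistent with a standardised effect size of 0.3", "a correlation between the four repeated measures of 0.7" and an ICC of 0.03. From these it concludes that "a sample size of 214 per group is required". With 20 patients per practice (design effect 1.57) and 20% loss, it reaches 840 from 42 practices.

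The Updated sample size calculation notes that 53 practices are now recruiting, which lowers the average cluster size. It continues: "Assuming 14 patients per practice gives a design effect of 1.39". On otherwise unchanged assumptions the total becomes 744.

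The abstract, also current text, says "Target recruitment is 840 adults with and 840 without musculoskeletal pain". The all-comer section says "Recruiting 840 all-comers will give 90% power". The update does not mention all-comers.

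Under GP practice recruitment, the trial describes itself as "seeking practices of different sizes (small and large) and locations (urban and rural"). Randomisation is stratified by list size above or below 7900. Under Patient recruitment, consecutive patients are invited, with methods tailored to each practice.

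**The concern.** There are two linked problems.

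First, the formula behind 1.39 is exact only when every practice contributes the same number. Unequal contributions raise the design effect for the same average. The article expects variation, since it speaks of an average and recruits practices of different sizes, but it gives variation no term. This formula is also what takes 96 patients off the requirement (840 - 744).

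Second, two musculoskeletal figures stand side by side. Recruitment was still under way at submission, so it matters which of them governs.

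At stake is whether 744 delivers the stated 90%. Any loss would fall unevenly on the two primary outcomes. Table 2 shows pain intensity measured at enrolment, so baseline adjustment may recover power for pain. Enablement is measured only after the consultation, so it has no baseline score to help.

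**Working it through.** **Inputs from the article.** Alpha 0.025, power 90%, standardised effect 0.3, four measures correlated 0.7, ICC 0.03, 20% loss, 14 patients per practice, 53 practices. Sidedness is not stated; two-sided reproduces the article's figure. **Assumed here:** CV of cluster size, shown from 0 to 0.8.

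**Reproducing the plan.**
- Repeated-measures factor: (1 + 3×0.7)/4 = 0.775.
- n per group: 2×((2.2414 + 1.2816)/0.3)² × 0.775 = 275.8 × 0.775 = 213.7, rounded up to 214.
- Design effects: 1 + 19×0.03 = 1.57 and 1 + 13×0.03 = 1.39.
- Totals: 428×1.57/0.8 = 839.95, giving 840; 428×1.39/0.8 = 743.65, giving 744.

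Every stated figure reproduces.

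**Allowing for unequal clusters.** DE = 1 + ((1 + CV²)m - 1)×ICC. The effective number per group is n = 744×0.8/(2×DE) = 297.6/DE. Power = Φ(0.3/√(2×0.775/n) - 2.2414).

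Worked example at CV 0.65 and m = 14: DE = 1 + (1.4225×14 - 1)×0.03 = 1.567; n = 189.9; power = Φ(3.320 - 2.241) = 86.0%.

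The plan puts the recruited size (14) in the design effect and then inflates for loss. The analysed average after 20% loss is 14×0.8 = 11.2, so both bases are shown.

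| CV | DE, m = 14 | Power at 744 | Total for 90% | DE, m = 11.2 | Power at 744 |
|---|---|---|---|---|---|
| 0 | 1.390 | 90.05% | 744 | 1.306 | 91.9% |
| 0.4 | 1.457 | 88.5% | 780 | 1.360 | 90.7% |
| 0.5 | 1.495 | 87.7% | 800 | 1.390 | 90.1% |
| 0.65 | 1.567 | 86.0% | 839 | 1.448 | 88.7% |
| 0.8 | 1.659 | 83.8% | 888 | 1.521 | 87.1% |

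On the analysed-size basis, a CV of 0.5 is offset exactly, because 11.2×1.25 = 14.

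**How firm that cushion is.** It keeps ICC 0.03 for an outcome whose variance has already been cut to 0.775 by averaging visits. If 0.03 is a single-visit ICC and the practice effect is stable over visits, the ICC of the averaged outcome is 0.03/0.775 = 0.0387. With m = 11.2, power at 744 is then 89.9% at CV 0, and 88.4%, 87.5%, 85.7% and 83.5% at CV 0.4, 0.5, 0.65 and 0.8. That is close to the m = 14 column. The article does not say which ICC it means.

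**The same check on 840.**
- From 42 practices (m = 20): 88.1% at CV 0.4 and 84.8% at CV 0.65.
- From 53 practices (840/53 = 15.8), with the recruited size in the design effect: 92.4% at CV 0, 90.1% at 0.5 and 88.5% at 0.65.

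**The case against.** The strongest reply is that nothing has been miscalculated and that the plan has slack elsewhere. Much of this stands.

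- The arithmetic is right. The article describes a falling average cluster size, and 53×14 = 742, so 14 is an average. A reader might infer that the plan expects every practice to recruit exactly 14; the text does not say so. The formula merely leaves variation out.
- A reader might conclude that 744 gives 84–88% power rather than 90%. The article does not support that as a fact. With m = 14 it needs a CV between about 0.46 and 0.79, and with m = 11.2 between about 0.72 and 1.01. No CV is given, and variation in list size does not fix variation in numbers recruited.
- The ICC of 0.03 is called conservative. With 0.02 (an assumption), 744 gives 90.3% at CV 0.65 and 88.9% at 0.8. Also, the mixed model uses all observed data, so the 20% treated as lost may contribute in part.
- The omission is not peculiar to the update; the calculation for 42 practices shares it.
- The section is openly headed as an update, and nowhere does the article say that recruitment stops at 744. If 840 is still being recruited, most of the power question goes away.
- This is a condensed article, and the full protocol may hold a CV allowance and the target in force.

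What remains is that the update shows no margin on the plan's own basis, and that two current statements of the musculoskeletal figure are left unreconciled.

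**Conclusion.** The point holds in a conditional form. The 744 is correct for equal clusters and gives 90.05% there. If cluster sizes vary with a CV of 0.4 to 0.8, the loss is about 1.5 to 6 percentage points on the plan's recruited-size basis. With the analysed size and ICC 0.03 there is no loss up to CV 0.5, and about 1 to 3 points at CV 0.65 to 0.8. That second basis is only as good as the reading of 0.03 as the ICC of the visit-averaged outcome. All of this assumes the plan's effect size, correlation and retention, with a normal reference distribution.

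The unreconciled target needs no assumption: the abstract says 840, the update derives 744, and neither the status of 744 nor its reach to all-comers is stated. This is a gap in consistency and in a stated assumption, not an arithmetic error, and a definite failure to reach 90% is not shown.

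**What to change.** 1. State the recruitment target in force for each patient group, and say whether the update applies to all-comers. Bring the abstract and the sample size sections into line.
2. Recompute the design effect as 1 + ((1 + CV²)m - 1)×ICC, using the CV of patient numbers in practices already recruiting. State whether m is the recruited or analysed size and whether 0.03 is a single-visit ICC.
3. Then either restate the power at 744 with its CV, or keep the published 840. From 53 practices, 840 gives about 90% at CV 0.5 on the recruited-size basis.

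The cost is one recalculation, a few sentences and possibly a slightly less favourable power figure. Keeping 840 asks for no patients beyond the target already published.
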